## Abstract

**Background::**

To assess the arterial oxygen partial pressure (PaO_2_) at defined time points during preoxygenation and to compare high-flow heated humidified nasal oxygenation with standard preoxygenation using oxygen insufflation via a facemask for at least 5 minutes, before intubation during induction of general anesthesia.

**Methods::**

This randomized, single-blinded, prospective study will be conducted in patients undergoing head and neck surgery. After standard monitoring, the artery catheter at the radial artery or dorsalis pedis artery will be placed and arterial blood gas analysis (ABGA) for baseline values will be performed simultaneously. Each group will be subjected to 1 of 2 preoxygenation methods (high-flow nasal cannula or simple facemask) for 5 minutes, and ABGA will be performed twice. After confirming intubation, we will start mechanical ventilation and check the vital signs and perform the final ABGA.

**Discussion::**

This trial aims to examine the trajectory of PaO_2_ levels during the whole preoxygenation procedure and after intubation. We hypothesize that preoxygenation with the high-flow nasal cannula will be superior to that with the face mask.

**Study registration::**

This trial was registered with the Clinical Trial Registry (NCT03896906; ClinicalTrials.gov).

## Introduction

1

Preoxygenation before tracheal intubation is usually achieved by delivering oxygen via a facemask before induction of anesthesia. This potentially prolongs the time available for securing the airway before hypoxemia to approximately 6 minutes.^[1–5]^ After the patient loses consciousness, manual ventilation is usually performed using a facemask, until the tracheal intubation is confirmed. This period can be prolonged if tracheal intubation is attempted multiple times. However, facemask ventilation has traditionally been avoided due to the risk of gastric gas insufflation, which leads to increased intragastric pressure, and increases the risk of pulmonary aspiration of the gastric content. Moreover, if difficult mask ventilation is anticipated, facemask ventilation may not be possible at all. Moreover, 6 minutes of hypoxemia without mask ventilation may be insufficient for intubation and may be catastrophic in patients with difficult intubation.

An ideal preoxygenation protocol should extend the apnea period safely during induction of general anesthesia is essential, to prevent life-threatening events. The high-flow nasal cannula (HFNC), such as the OptiFlow System (Thrive, Fisher & Paykel, Auckland, New Zealand), has the ability to deliver warm and humidified oxygen through a specially designed nasal cannula, which enables comfortable oxygen delivery at rates >70 L/min.^[3,6–8]^ Several studies have showed that nasal delivery of humidified oxygen to paralyzed and anesthetized patients maintains oxygenation and achieves acceptable carbon dioxide concentrations.^[1–3,6,9–13]^ The study protocol involves a single-center, single-blinded, prospective, randomized controlled, and superiority trial, to prove the hypothesis that an extended apneic period with preoxygenation via the HFNC could be more beneficial to patients undergoing general anesthesia during induction compared with preoxygenation with a simple mask.

## Methods

2

### Study setting

2.1

The study protocol follows the standard protocol items: recommendation for interventional trials (SPIRIT) guidelines for reporting protocol items for randomized controlled trials (RCTs).^[14]^ The process of recruiting and enrolling the study population began in May, 2019 and is currently in progress at Asan Medical Center. Asan Medical Center is a tertiary academic hospital in Korea. The aim of the study is to assess arterial oxygen partial pressure (PaO_2_) at defined time points during preoxygenation and to compare the 2 methods, that is, preoxygenation with high-flow heated and humidified nasal cannula and standard preoxygenation with oxygen insufflation via a facemask. Assessments will be performed at baseline, 2 and 5 minutes, and immediately after intubation for each patient. Outcome assessors include the same anesthesiologist, who cannot be blinded. However, statisticians responsible for the final analysis will be blinded.

### Participants

2.2

#### Inclusion criteria

2.2.1

1)Patients with head and neck cancer undergoing resection surgery planned arterial cannulation and invasive arterial blood pressure monitoring and ABGA2)Patients aged between 19 and 80 years3)Patients who voluntarily participated in the study4)Patients with American Society of Anesthesia physical status 1 to 3

#### Exclusion criteria

2.2.2

1)Patients who did not wish to participate in the study2)Patients who were unable to give informed consent because of a language barrier3)Patients with severe respiratory disease4)Patients with severe cardiovascular or cerebrovascular disease5)Patients with severe psychiatric disorders6)Anyone considered inappropriate for participation by the researchers

### Assignment of intervention and common procedure

2.3

#### Randomization and blinding

2.3.1

Patients will be randomly assigned to 1 of 2 groups: the M group or the N group. The randomization scheme was generated using a web-based program (http://www.randomization.com), and the sequentially numbered assignments are blinded to which group each participant is assigned until just before surgery. Although the investigator could not proceed blinded due to the nature of the trial, the participants were blinded to the group assigned. An independent outcome assessor will be assigned as an investigator. Unblinding would not be needed until data analysis.

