#### Intervention (preoxygenation phase)

2.3.2

Group N (HFNC): Apply high-flow heated and humidified nasal oxygen with the OptiFlow System at a flow rate of 30 L/min and an inspiratory oxygen fraction (FiO_2_) of 1.0. Gradually increase the oxygen flow to 60 L/min over the course of the first 2 minutes. Ask the patients to not speak during anesthesia induction, to keep the mouth closed, and to breathe with their noses.

Group M (simple facemask): Perform standard preoxygenation by oxygen insufflation via a facemask using the standard anesthesia ventilators (semicircular system) with 100% oxygen flow of 12 L/min. The patients breathe at tidal volume.

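### The trial is called single-blinded with blinded participants, but conscious patients wear one of two plainly different devices, so participant blinding ends when the device goes on

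*Protocol article*

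**What the plan says.** - **Label.** The Methods part of the abstract reads: "This randomized, single-blinded, prospective study will be conducted in patients undergoing head and neck surgery". The Introduction repeats the single-blind description.
- **Who is blinded.** Section 2.3.1 (Randomization and blinding) attaches the label to the patients. It begins "Although the investigator could not proceed blinded due to the nature of the trial" and continues that "the participants were blinded to the group assigned". The same section keeps each assignment hidden until shortly before the operation.
- **Assessors and statisticians.** Section 2.1 (Study setting) says "Outcome assessors include the same anesthesiologist, who cannot be blinded", followed by "However, statisticians responsible for the final analysis will be blinded". Section 2.3.1 says "An independent outcome assessor will be assigned as an investigator".
- **What patients experience.** For group N, section 2.3.2 says "Apply high-flow heated and humidified nasal oxygen with the OptiFlow System at a flow rate of 30 L/min", rising to 60 L/min, and tells staff: "Ask the patients to not speak during anesthesia induction, to keep the mouth closed, and to breathe with their noses". Group M breathes oxygen at 12 L/min through a facemask. Section 2.3.3 sets 5 minutes of preoxygenation, puts T1 and T2 ahead of the anesthetic, and foresees patients being distressed by a tight mask.
- **What patients know.** Section 2.7.2 has the purpose and procedure explained before consent.
- **Outcomes.** Section 2.4 makes PaO2 primary, patients' discomfort secondary and the anesthesiologists' satisfaction tertiary.

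**The concern.** The article states a design property that its own procedures cannot deliver. A reader who sees a single-blind trial with blinded participants will assume that anything patients report was given without knowledge of the treatment. Here the patient's own report concerns the comfort of the device on the face, so knowledge of the device is complete. The trial also expects the nasal cannula to do better, and patients are told the purpose of the study. A discomfort result presented as blinded would therefore carry more credibility than the design gives it. A secondary problem is that two sections describe the outcome assessor differently, so a reader cannot tell who records what.

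**Working it through.** The article gives no figure on this point, so the check sets its statements side by side.

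**1. Are patients conscious while the devices are in use?** Yes. Preoxygenation runs for 5 minutes, and the T1 (2 minutes) and T2 (5 minutes) samples precede the anesthetic (2.3.3). Group N patients are also given breathing instructions to follow (2.3.2).

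**2. Can they tell the devices apart?** Yes. One is a nasal cannula with heated, humidified flow of 30 to 60 L/min and a closed mouth. The other is a facemask at 12 L/min. They differ in position, sensation and instructions, and no sham or masking device is described.

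**3. Could they recognise the device without knowing what it means?** This is unlikely, because the purpose and procedure are explained before consent (2.7.2). The article does not describe withholding the comparison from patients.

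**4. Does concealment until just before surgery rescue the claim?** No. It protects the assignment up to the start of the procedure. Every value after T0 is obtained once the device has been applied.

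**5. Which outcomes depend on the patient's knowledge?**

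| Outcome (2.4) | Source | Effect of the mistaken claim |
|---|---|---|
| PaO2 and other blood gas values | Blood gas analysis | Little |
| SpO2, EtO2, EtCO2, heart rate, blood pressure | Monitor | Little |
| Apnea time, laryngoscopy attempts, rescue maneuvers | Operator or recorder | None from the patient claim; operator declared unblinded |
| Performers' satisfaction | Operator | None from the patient claim; operator declared unblinded |
| Patients' discomfort | Patient's experience of the device | Direct |

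The mistaken claim therefore misleads on essentially one listed outcome.

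**6. Do the assessor statements agree?** Section 2.1 says the assessors include the unblindable anesthesiologist. Section 2.3.1 speaks of an independent assessor but makes that person an investigator, in a paragraph that says the investigator could not work blinded. Both can be true if there are two assessors with different tasks, but the article does not divide the tasks.

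**7. Does any planned number change?** No. The sample size in section 2.5 rests on PaO2 means and standard deviations, alpha and power. None of these depends on who is blinded.

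**The case against.** The best defence is that the article is open about most of this. It says that the investigator and the anesthesiologist cannot be blinded, it keeps the allocation concealed, and it blinds the statisticians. The primary outcome is a laboratory value. A discomfort rating about a device can hardly be separated from knowing which device it is, so no feasible design would have blinded it. All of that stands, and it limits the consequence. It does not save the sentence about participants, which is wrong from the moment the device is applied.

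Two stronger readings are tempting.

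- **That the article claims a blinded assessor and then contradicts itself.** It does not. Section 2.1 says the assessors include the anesthesiologist, which leaves room for another. Section 2.3.1 calls its assessor independent, not blinded. The roles are unclear and need reconciling, but no assessor blinding is promised.
- **That none of the claimed protection exists.** This is too broad. Statistician blinding and concealment of the allocation are both stated, and nothing in the procedures defeats them.

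**Conclusion.** The claim of participant blinding does not hold and should be corrected. Once the device is applied, effectively no patient is blind to it. The consequence falls mainly on patients' discomfort. Its size and direction cannot be computed, because the article gives no data on how knowledge of the device shifts such a rating.

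A reader might extend the point to the anesthesiologists' satisfaction, rescue use, flow reductions, mask loosening or exclusions for non-cooperation. Those are judged or decided by staff whom the article already declares unblinded. Blinding the patients would not have protected the operators' own judgments, so the mistaken claim does not mislead there. Nor do the documents support a charge that the PaO2 comparison is compromised by the label.

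The conclusion rests on two assumptions: that discomfort reflects the patient's own experience of the device while conscious, since the article does not say how or when it is collected; and that no masking of the devices is used beyond what the article describes.

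**What to change.** - In the abstract, the Introduction and section 2.3.1, replace the single-blind label and the sentence on participants with a factual statement: open-label, allocation concealed until just before surgery, and statisticians blinded for the final analysis, as section 2.1 already says.
- State that patients' discomfort is an unblinded rating, and report and interpret it as such.
- Reconcile sections 2.1 and 2.3.1 by stating which assessor, the unblinded anesthesiologist or an independent investigator, records which outcome, without claiming blinding for either. The division of tasks is for the investigators to state; the article does not settle it.

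The registry entry is not available here, so whether its masking field needs the same correction cannot be judged.

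**Cost.** Only wording changes. Procedures, staffing, sample size and the PaO2 analysis stay as they are. The trial loses its single-blind label, and the discomfort comparison carries less weight.

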#### Intervention (preoxygenation phase)

2.3.2

Group N (HFNC): Apply high-flow heated and humidified nasal oxygen with the OptiFlow System at a flow rate of 30 L/min and an inspiratory oxygen fraction (FiO_2_) of 1.0. Gradually increase the oxygen flow to 60 L/min over the course of the first 2 minutes. Ask the patients to not speak during anesthesia induction, to keep the mouth closed, and to breathe with their noses.

Group M (simple facemask): Perform standard preoxygenation by oxygen insufflation via a facemask using the standard anesthesia ventilators (semicircular system) with 100% oxygen flow of 12 L/min. The patients breathe at tidal volume.

#### Common procedure applied to all subjects

2.3.3

Standard monitoring including pulse oximetry (SpO_2_), 3-lead electrocardiogram (EKG), and noninvasive blood pressure will be performed. After local anesthesia, the artery catheter will be inserted into the radial artery or dorsalis pedis artery, with simultaneously baseline ABGA (T0) monitoring. After recording the data from the ABGA and initial vital signs, preoxygenation for a given group will be performed for 5 minutes. Recording of ABGA and the vital signs will be performed at the predefined time points (T1 and T2), before anesthesia injection. Endotracheal intubation will be attempted about 2 minutes after injection of anesthetics and muscle relaxants. After confirming intubation, mechanical ventilation will be started, and the vital signs and last ABGA (T3) will be recorded. The flow diagram of all the study measures is shown in Fig. 1. If the saturation recorded by the pulse oximeter falls below 90% during the procedure, the trial will be stopped immediately. If a patient from group N experiences intolerable discomfort during the course of the trial, the flow rate will be reduced to an acceptable level and recorded. If a patient from group M experiences extreme frustration because of the tight mask, the fitting should be released slightly and record. If appropriate actions are taken for each patient and he/she does not cooperate, he/she will be excluded, even if he/she has consented to participating in the study.

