#### Defined time points

2.3.4

T0: preinduction baselineT1: 2 minutes after preoxygenationT2: 5 minutes after preoxygenationT3: at the second tidal volume with mechanical ventilation after intubation

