### Outcomes

2.4

The primary outcome is PaO_2_ at the predefined time points.

The secondary outcomes include patients’ discomfort, end-tidal oxygen saturation (EtO_2_) at T0 and T3, EtCO_2_ at T0 and T3, other data from ABGA (eg, PaCO_2_, pH, base excess, and HCO_3_), apnea time, SpO_2_, and other vital signs (heart rate, arterial blood pressure).

The tertiary outcomes include the patients’ upper airway condition including the modified Mallampati score, upper lip bite test, thyromental distances and the presence of a mass within the upper airway tract, indication for surgery, seniority of the anesthesiologist, the number of attempts at laryngoscopy, use of any rescue maneuvers, and performers’ (anesthesiologists) satisfaction.^[10,15]^ Apnea time is defined the period from the time of propofol injection till the tracheal tube is secured.

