### Sample size and recruitment

2.5

To determine the sample size for the study, we used previously published data^[9]^ showing that 5 minutes of preoxygenation with HFNC achieved a median of 406 (Q2: 362; Q3: 446) mm Hg, and 5 minutes of facemask preoxygenation achieved a median PaO_2_ of 335 (Q2: 292; Q3: 389) mm Hg. Estimated mean (SD) PaO_2_ achieved with the HFNC and simple mask are 339 (82.3) mm Hg and 405 (71.3) mm Hg, respectively. This yielded a sample size of 23 participants per group, with alpha = 0.05 and power = 0.8.^[16]^ We need 26 participants per group (total 52), after accounting for 10% screen failure. We used a program called G∗Power Version 3.1.7 (Kiel University, Germany) to calculate the sample size.

Patients will be recruited on the day before surgery, once the surgery is planned and the date is scheduled. As soon as sufficient explanation is provided and consent for clinical trials is obtained, they will be assigned to a randomized trial group. After arriving at the operating room for surgery, a monitor for general anesthesia will be started and the clinical trial will be also initiated. There will be no additional visit dates for the participants, as the clinical trial will be terminated as soon as the induction of general anesthesia is completed. Efforts will be made to screen and select the appropriate participants for clinical trials, to recruit participants, and to meet the target sample size.

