### Data collection management and analysis

2.6

After the examiner or the person designated by the examiner receives approval from the institutional review board (IRB), the participants’ data will be collected. To obtain accurate data, the outcome assessors have been given sufficient training, before conducting the trial, and the case report form (CRF) includes pictures and examples for objective assessment of the airway. The collected data should be stored in the original locked location, and access to the data is available only to the responsible investigator and investigators authorized by him.

To compare data between the groups, the chi-square test or Fisher exact test will be used to assess categorical variables. Student *t* test or the Mann–Whitney *U* test will be used to analyze continuous variables, as appropriate. All data manipulations and statistical analyses will be performed using SPSS for Windows, version 21 (IBM Corp, Armonk, NY) and Stata software version 13.1 (StataCorp LP, College Station, TX). Statistical analysis for the missing data will be adjusted with an estimating equation or statistical model in the final analysis. A 2-tailed *P* value of <.05 will be considered to indicate a statistically significant difference.

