#### Adverse events

2.7.1

The investigator should institute appropriate therapeutic and follow-up measures in accordance with good medical practices and should record them in the participant's CRF. The study does not include a data monitoring committee (DMC), but an interim analysis can be made by the investigator responsible, and it will only be made if there is a significant clinical difference between the 2 groups and significant statistical differences could lead to early termination of trial.

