## Discussion

3

Preoxygenation with an HFNC during induction of general anesthesia has recently become an appealing option to anesthesiologists.^[3,6,9–12]^ This trial primarily aims to examine the trajectory of PaO_2_ levels during the whole preoxygenation procedure before and after intubation. We expect that the preoxygenation with HFNC will prove superior to the classical method with facemask, during the preinduction period of general anesthesia. To maintain the quality of this study and arrive at a reliable conclusion, the experimental design method and the research results will go through strict quality control. We will use the CONSORT checklist for the experimental design.^[17]^ The main strength of our protocol is that the study population consists of patients with head and neck cancer, who are more likely to have a difficult airway.

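### The stop at SpO2 below 90% does not secure the T3 blood gas, so a primary-outcome PaO2 can go missing because oxygenation was poor

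*Protocol article*

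**What the plan says.** Section 2.3.3 of the protocol article sets the safety rule: "If the saturation recorded by the pulse oximeter falls below 90% during the procedure, the trial will be stopped immediately". The same section places the final blood gas later in the sequence: "After confirming intubation, mechanical ventilation will be started, and the vital signs and last ABGA (T3) will be recorded". Section 2.3.4 defines T3 as "at the second tidal volume with mechanical ventilation after intubation".

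Section 2.4 makes T3 part of the primary outcome: "The primary outcome is PaO_2_ at the predefined time points". The Discussion gives the primary aim as to "examine the trajectory of PaO_2_ levels during the whole preoxygenation procedure before and after intubation".

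The word *trial* has two senses in the article. Section 2.5 uses it for one participant's procedures: "the clinical trial will be terminated as soon as the induction of general anesthesia is completed". Section 2.7.1 uses it for the whole study: "significant statistical differences could lead to early termination of trial".

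Two other statements bear on the point. Section 2.6 says "Statistical analysis for the missing data will be adjusted with an estimating equation or statistical model in the final analysis". Section 2.4 lists use of rescue maneuvers as a tertiary outcome and apnea time, which runs until the tube is secured, as a secondary one. Section 2.3.3 speaks of exclusion only for patients who do not cooperate.

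**The concern.** The trigger for stopping is low oxygen saturation, and the measurement that may be lost is arterial oxygen pressure. If staff take the rule at its word and end study procedures for a patient who desaturates during apnea, the one blood gas still to come is T3. The T3 comparison would then be made only among patients who stayed at or above 90%. The missingness would depend on a variable closely tied to the outcome.

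The direction depends on the arm. Omitting low values from the mask arm would understate an HFNC benefit after intubation; omitting them from the HFNC arm would overstate it. T3 is the only sample taken after apnea, and the Introduction's hypothesis concerns an extended apneic period, so the rule touches a comparison that readers will look at.

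This is a matter of conduct as well as analysis: a blood gas that was never drawn can only be replaced by assumption.

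**Working it through.** **1. Order of events (sections 2.3.3 and 2.3.4).** T0 baseline → T1 at 2 minutes → T2 at 5 minutes → injection of anesthetics and muscle relaxants → intubation attempted about 2 minutes later → ventilation → T3. T1 and T2 are taken before injection. A stop after injection therefore leaves T0 to T2 intact and can affect only T3 and the other post-intubation measures.

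**2. What stopping means.**
- Per patient (the usage in section 2.5): remaining study procedures end, and the only remaining blood gas is T3. Selective loss is possible.
- Whole study (the usage in section 2.7.1): no per-patient selection at T3 follows, but one desaturation would close a 52-patient trial. That is an unlikely intention.

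The per-patient reading is the natural one. Under it the text neither orders T3 to be skipped nor says that it is drawn. A patient who is rescued and intubated still reaches the second ventilated breath with an arterial line in place, so the sample remains feasible.

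**3. The plan's own figures (section 2.5).** The stated means (SD) are 339 (82.3) and 405 (71.3) mm Hg, for the 5-minute value.
- Which arm is which: averaging the three quoted quantiles gives (292 + 335 + 389)/3 = 338.7 for the mask and (362 + 406 + 446)/3 = 404.7 for HFNC. I therefore take mask = 339 and HFNC = 405, although the sentence giving the means names the arms in the opposite order. This does not affect the sample size.
- Difference: 405 − 339 = 66. Pooled SD: √((82.3² + 71.3²)/2) = 77.0.
- A two-sided t test at 0.05 has power 0.793 with 22 per group and 0.811 with 23, so the stated 23 reproduces. 23/0.9 = 25.6, rounded up to 26, also reproduces.

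**4. Effect of one omitted T3 (illustration).** Let m be the mean of the other 25 patients in an arm and x the T3 value left out. The full mean is (25m + x)/26, and the mean without the patient is m. The shift is (m − x)/26.

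Assumptions not given in the document: m equals the 5-minute planning mean, and x lies between 60 mm Hg (not recovered) and m (fully recovered by rescue).

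| x (mm Hg) | Mask arm, m = 339 | HFNC arm, m = 405 |
|---|---|---|
| 60 | 279/26 = 10.7 | 345/26 = 13.3 |
| 100 | 239/26 = 9.2 | 305/26 = 11.7 |
| 200 | 139/26 = 5.3 | 205/26 = 7.9 |
| m | 0 | 0 |

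The upper ends are 10.7/66 = 16% and 13.3/66 = 20% of the planning difference. One such omission in each arm nearly cancels: (345 − 279)/26 = 2.5 mm Hg net.

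For scale, the planning standard error of the difference is √((82.3² + 71.3²)/26) = 21.4 mm Hg, so a single omission shifts the result by less than one standard error.

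**The case against.** The strongest reply is that the finding rests on silence in a condensed article. T3 is described under a heading that covers all subjects, exclusion is reserved for non-cooperation, and outcomes such as rescue maneuvers and apnea time suggest that recording continues through difficult inductions. Section 2.6 provides for missing data, and an analysis plan could rank stopped patients lowest without any T3 value. Stops should be rare: severe respiratory and cardiovascular disease is excluded, and intubation is attempted about 2 minutes after injection. Even the extreme illustrative shift lies below one standard error.

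Much of this stands. It makes the point minor and limits it to T3. It does not remove it. The objection is to a rule that the article does state, and that rule can be followed in a way that loses the sample. Listing rescue maneuvers as an outcome shows that such patients are recorded, not that T3 is drawn. The missing-data sentence names no model or assumption and does not mention stopped patients; any model for a loss triggered by poor oxygenation would rest on assumptions that cannot be tested. A lowest-rank test works without T3, but only if the patient is kept, and it gives no PaO2 value for the trajectory that the trial sets out to describe. Nor can the absence of events be taken for granted: the Discussion presents the population as more likely to have a difficult airway.

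A reader might go further and infer that the protocol prescribes omitting T3, or removes desaturated patients from the analysis. The text says neither.

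**Conclusion.** The point holds in a limited form. The rule, read per patient and followed literally, permits T3 PaO2 to be missing because oxygenation was poor, and nothing else in the article ensures that the sample is taken. After induction, only the T3 comparison is at risk; T1, T2 and the sample-size basis are untouched.

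The document gives no desaturation rate and no T3 values, so the total bias and its direction cannot be determined. It is zero if nobody is stopped or if T3 is drawn and kept. The range of 0 to about 11 mm Hg (mask) or 13 mm Hg (HFNC) per omitted patient is an illustration that depends on using 5-minute means for T3 and on the assumed value of the omitted sample. It would be wrong to infer from it that the trial is biased by that amount, or that the result is tilted toward HFNC.

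Minor severity: a cheap improvement. The safety stop itself is proper and should stay.

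**What to change.** Amend section 2.3.3 to say that:

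1. SpO2 below 90% ends the assigned oxygenation method for that patient and triggers rescue. It neither excludes the patient nor closes the study.
2. The planned T3 sample is still drawn at the second ventilated breath, once the patient is intubated and it is safe, and is flagged as post-rescue.
3. The patient stays in the randomized comparison.
4. The number of patients with SpO2 below 90% is reported by arm.
5. One T3 sensitivity analysis ranks these patients lowest in a Mann-Whitney test, which is already among the planned tests.

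The cost is a short amendment and one extra analysis. No extra blood sample is needed, because T3 is already planned and the arterial line is in place. The downside is that a post-rescue T3 mixes the effect of the assigned method with that of the rescue; the lowest-rank analysis is there to address this. The change is best made soon: section 2.1 says that recruitment is under way, and a T3 missed in the meantime cannot be taken later.

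### Randomised patients who still do not cooperate after their device is adjusted are excluded, an exclusion linked to the assigned arm that can bias the PaO2 and discomfort comparisons in either direction.

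*Protocol article*

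**What the plan says.** All references are to the protocol article.

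- **Adjustment comes first (section 2.3.3).** For intolerable discomfort in group N, "the flow rate will be reduced to an acceptable level and recorded". For the mask arm, "If a patient from group M experiences extreme frustration because of the tight mask, the fitting should be released slightly and record". In both cases the patient continues.
- **Exclusion comes second (section 2.3.3).** A patient for whom this has been done, but who still "he/she does not cooperate, he/she will be excluded, even if he/she has consented to participating in the study".
- **Timing of assignment (section 2.5).** Recruitment is on the day before surgery. "As soon as sufficient explanation is provided and consent for clinical trials is obtained, they will be assigned to a randomized trial group".
- **Blinding (section 2.3.1).** "Although the investigator could not proceed blinded due to the nature of the trial". Section 2.1 blinds the statisticians, but they do not decide who is excluded.
- **Outcomes (section 2.4).** "The primary outcome is PaO_2_ at the predefined time points". Patient discomfort is the first secondary outcome listed.
- **Allowance (section 2.5).** "We need 26 participants per group (total 52), after accounting for 10% screen failure".
- **Missing data (section 2.6).** An estimating equation or a statistical model, not further specified, is to be used. It is not linked to excluded patients.

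**The concern.** The design is a "single-center, single-blinded, prospective, randomized controlled, and superiority trial", and its comparison rests on the two groups being alike apart from the device. The exclusion rule acts after assignment and after the device has been applied. What leads to it differs by arm (discomfort from high flow in one, a tight mask in the other), the person applying it knows the arm, and no criterion for non-cooperation is given. Losses may therefore differ between arms in number and in kind.

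Cooperation is also part of the delivered treatment. Section 2.3.2 asks group N patients to keep the mouth closed, not to speak and to breathe through the nose. A link between non-cooperation and PaO2 is plausible, though the article gives no data on it. Discomfort is affected more directly, because a patient who still refuses after adjustment is likely to be among the worse cases on that outcome.

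At stake are the primary PaO2 difference, which could be pushed either way depending on which device loses more patients, and a discomfort comparison from which some of the worst cases have been removed.

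**Working it through.** **1. The plan's own figure.** Section 2.5 gives means (SD) of 339 (82.3) and 405 (71.3) mm Hg, alpha 0.05 and power 0.8. Section 2.6 makes the test two-sided.

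- Difference: 405 − 339 = 66 mm Hg.
- Pooled SD: √[(82.3² + 71.3²)/2] = 77.0.
- Standardised difference: 66/77.0 = 0.857.
- Two-sample t test (noncentral t): n = 22.4, rounded up to 23 per group.
- With 10%: 23/0.9 = 25.6, rounded up to 26 per group.

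Both 23 and 26 reproduce. Power with 26 per group is 0.858, so the point does not rest on a sample-size error. Below, the mask arm is taken as 339 (82.3) and the HFNC arm as 405 (71.3). This follows the medians in the same section (335 for mask, 406 for HFNC); the sentence with the means names the arms in the opposite order.

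**2. Bias from excluding part of one arm.** Let a share e of an arm be excluded, and let those patients' PaO2 lie D mm Hg below that of the patients kept. The arm mean then rises by e × D. The article gives neither e nor D, so both are assumptions.

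- 1 of 26, D = 50: 0.038 × 50 = 1.9 mm Hg (3% of 66).
- 2 of 26, D = 100: 0.077 × 100 = 7.7 mm Hg (12%).
- 5 of 26, D = 150: 0.192 × 150 = 28.8 mm Hg (44%).

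**3. Two of 26 lost: planned difference and power.** Simulated with 26 randomised per arm and a two-sided t test at 0.05. Tolerance is correlated with PaO2 as shown, and the two least tolerant patients are dropped. In the extreme case they are the two with the lowest PaO2.

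| Two patients lost from | Link to PaO2 | Mean difference (mm Hg) | Power |
|---|---|---|---|
| nobody | – | 66 | 0.86 |
| mask only | correlation 0.3 | 62 | 0.81 |
| mask only | correlation 0.5 | 60 | 0.78 |
| mask only | two lowest | 54 | 0.73 |
| HFNC only | two lowest | about 77 | 0.94 |
| both arms | two lowest | 64 | 0.87 |

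The extreme rows can be checked with the truncated-normal shift, SD × φ(z)/(1 − q), where q = 2/26, z = −1.426 and φ(z) = 0.144.

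- Mask: 82.3 × 0.144/0.923 = about 13, so 66 − 13 = 53.
- HFNC: 71.3 × 0.144/0.923 = about 11, so 66 + 11 = 77.

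**4. Type I error with no true difference (SD 77, two lost from one arm only).**

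- Correlation 0.3: false difference 3.4 mm Hg, error 5.3%.
- Correlation 0.5: 5.6 mm Hg, 6.0%.
- Two lowest: about 11 mm Hg, about 9.4%.

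**5. Loss of numbers alone.** Losing 3 per arm at random leaves 23 per arm and power 0.81. Losing 4 leaves 22 and 0.79. The extra patients absorb that loss of precision but do not correct bias.

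**The case against.** Four objections deserve an answer.

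- **Intolerance alone does not exclude.** A reader might infer that everyone who tolerates the device badly is dropped, so that treatment failures as a class disappear. The text does not support this. Adjustment comes first, it is recorded, and a patient who accepts it stays. The rule reaches only those who still refuse, who may be few in a five-minute phase. This objection stands, and the point is limited accordingly.
- **Exclusion might mean leaving the procedure, not the analysis.** The sentence sits in the procedures section. Analysis sets are commonly left to a full protocol or SAP, which is not shown, so the lack of an intention-to-treat statement is not held against the article. But this is a rule that is stated, not a silence. Its plain reading is removal from the study, and nothing in the article points the other way. If the narrower meaning is intended, one sentence settles it.
- **The largest figures need an extreme assumption.** They require that the excluded patients have the very lowest PaO2 and come from one arm only. No passage shows that non-cooperative patients are the low responders. This also stands: under moderate assumptions the effect is small. Nor is the harm simply lost power, since losses from the HFNC arm enlarge the apparent benefit.
- **The 10% gives room.** A reader might infer that nothing covers these losses. In number that is not so, because 26 against 23 leaves three spare patients per arm. The label is still wrong for this purpose: screen failures occur before randomisation, and spare patients do not remove selection.

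**Conclusion.** The concern holds in this limited form. As written, section 2.3.3 removes some randomised patients because of their reaction to the assigned device, on the judgement of staff who know the arm. Neither the unspecified missing-data model in section 2.6 nor the 10% allowance offsets this.

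The size cannot be known from the article. If 2 of 26 are lost from one arm, the bias is about 3 to 6 mm Hg under a moderate link with PaO2 and about 11 to 13 mm Hg in the extreme case, against a planned 66. Type I error is then about 5–6% and about 9.5% respectively. The direction depends on which arm loses patients. If losses are rare or balanced, the effect on the difference is small. What is established is a fault in the rule, not that the result will be materially biased.

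**What to change.** - State in section 2.3.3 that non-cooperation ends study procedures only, and that the patient stays in the primary analysis in the arm to which he or she was randomised.
- Use all ABGA and discomfort data already obtained. A patient who refuses or withdraws may have no T1, T2 or T3 sample, so state that the missing-data model of section 2.6 covers these values.
- Record non-cooperation and its time, report it by arm, and use the cooperative-only set as a sensitivity analysis.
- Relabel the 10% (23 to 26 per group) as an allowance for data lost after randomisation.

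The cost is amendment wording and some missing-data modelling. The number stays at 26 per group, and the estimated effect may be slightly smaller. No change to the clinical handling of these patients is proposed. Section 2.1 says that enrolment is under way, so the change is best made before more patients are excluded and before the data are analysed.
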